### Randomization

After obtaining informed consent, randomization will be carried out by trained research assistants in the two study centers using a centralized web-based tool (Randomizer Software, Institute for Medical Informatics, Statistics and Documentation of the Medical University of Graz, www.randomizer.at). Block randomization is applied to guarantee equal sample sizes in each group in case the planned sample size is not achieved. The block size is specified in the web-based tool by the study coordinator and cannot be seen by physicians enrolling participants or research assistants assigning interventions. The allocation ratio for IG and CG is 1:1. Randomization is stratified by the study center. Due to the nature of this trial, blinding of the patients and physicians is not feasible.

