#### Key secondary outcomes

We will use the German version of the *Satisfaction with Decision Scale* (SwD [40];), extracted from Härter et al. [41], to assess patient decision satisfaction. The scale’s scores range between 6 and 30, with higher scores indicating higher satisfaction with specific health care decisions. As hypothesis 2 refers to decision satisfaction in the further course of the treatment, patient satisfaction at T_2_, i.e., approx. 3 months after the decision, will be analyzed. For further analyses, satisfaction with decisions will be additionally assessed directly after the intervention (T_1_).

Moreover, to test hypothesis 3, a validated German version [42] of the *Observer OPTION-5 scale* [43] will be applied. The Observer OPTION-5 scale is a rater-based observing method to assess SDM regarding a specific health care decision. The scale contains 5 criteria for SDM efforts on the part of the physician that two blinded, independent, trained raters classify on a scale from 0 (*no effort*) to 4 (*exemplary effort*) using audio recordings and transcripts of the medical consultations. The mean value of both raters will be used. The German version of the Observer OPTION-5 has an excellent overall interrater reliability of .82 [42].

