### Statistical analysis

#### Sample size

A power analysis was conducted with GPower version 3.1.9.2 with patients’ knowledge about first-line treatment options at T_1_ as the main outcome for the effectiveness of the intervention. According to a Cochrane review, PtDAs improve the level of knowledge with an effect size of *d* = 0.60 [25]. On the basis of a group comparison (*t* test for independent samples) and an *α* error of 5% (two-sided), a case number of *n* = 45 participants per group (total = 90) is sufficient to detect a statistically significant effect of *d* = 0.6 with a power of 80%. To compensate for an assumed drop-out rate of approximately 40%, we plan to include 128 patients in the study.

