#### Main analyses

All main analyses are based on the intention-to-treat (ITT) population, which includes all randomized patients except those who withdraw informed consent. Missing values will be assumed to be *missing at random* and replaced by multiple imputation using the *fully conditional specification method* [47]. When imputing multi-item instruments, imputation will be performed at the item level, and the total score will be calculated based on the imputed items [48]. Additionally, as sensitivity analyses, the results obtained for the ITT population will be compared to the results of a sample including only complete cases and to the results of a sample including only complete cases without serious protocol violations (per-protocol analysis).

All analyses will be carried out with SPSS 24. Descriptive analyses will be performed to describe sample characteristics.

Multiple linear regression analyses will be carried out to test the three hypotheses described. To test the main hypothesis, the influence of group membership (IG vs. CG) on the patient’s level of knowledge at T_1_ will be analyzed. The model controls for the following covariates: patient’s level of knowledge at T_0_, age, level of education, and study center.

Secondary outcomes will be analyzed using similar regression models. Additionally, to consider the usefulness of the PtDA from a provider perspective, group differences between physicians educating patients of the IG and the CG will be analyzed in terms of the physicians’ emotional and cognitive strain using the Mann-Whitney *U* test.

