As described above, the evaluation of the PtDA is to be carried out in a multicenter, randomized, controlled study design and comprises several measurement points (T_0_, T_1_, T_2_), since the influence of SDM in general, and presumably of PtDAs in particular, on patient satisfaction can only be expected over the long term [30]. Patients with access to the PtDA before the medical consultation will be compared with patients who receive treatment as usual. The study design is thus adapted to clinical care processes. On the one hand, this guarantees high external validity. On the other hand, this means that the study procedure cannot be extensively standardized. For example, we expect variations in the course of the medical consultation. Sources of this variance are physician-related variables (e.g., professional experience), patient-related variables (e.g., BRAF status), and setting-related variables (e.g., if including the patient in a drug trial is available as an additional option to the standard therapies). Additionally, different progressions after the decision for one treatment option between patients must be considered. It is possible, for example, that a patient may have to discontinue the selected therapy due to severe adverse events, and the follow-up survey T_2_ may therefore have to take place earlier. A further limitation of the design is the lack of the possibility of blinding group membership.

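### Physician strain is compared between arms with an unstratified Mann-Whitney test although each physician probably rates several consultations in both arms; the likely cost is lost power, with no protection if physicians are unevenly spread over the arms

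*Protocol article*

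**What the plan says.** All references are to the protocol article.

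- **Strain, outcome** (Further secondary outcomes): the physician answers two 5-point items, one cognitive and one emotional, about the consultation just held. The unit of measurement is the consultation.
- **Strain, analysis** (Main analyses): "group differences between physicians educating patients of the IG and the CG will be analyzed in terms of" emotional and cognitive strain, using a Mann-Whitney U test. No stratification or handling of repeated raters is given.
- **SDM, outcome** (Key secondary outcomes): "The scale contains 5 criteria for SDM efforts on the part of the physician", scored by two blinded raters.
- **SDM, analysis** (Main analyses): multiple linear regression. The model for the main hypothesis carries baseline knowledge, age, education and centre. Secondary outcomes get similar models with covariates not listed. No physician term is named.
- **Allocation** (Randomization): by patient, 1:1, in blocks. "Randomization is stratified by the study center". Physician is not a stratification factor.
- **Physician variation**: the Discussion expects consultations to vary and says "Sources of this variance are physician-related variables (e.g., professional experience" among others. Treatment as usual says the consultation depends on the physician's communication style. Further measurements lists basic physician characteristics among possible covariates, without tying them to a model.

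**The concern.** A Mann-Whitney test compares two sets of independent observations. The protocol describes those sets as physicians of the two arms, but physicians are not what is randomised. With up to 128 consultations at two centres, a physician will almost certainly rate more than one. Because allocation is by patient within centre, that physician will probably rate patients of both arms. Ratings by one physician share that person's rating habits, and OPTION-5 scores share that person's consultation style.

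Two things are at stake. First, differences between physicians stay in the noise when they could be removed, which costs power for the provider outcome and for hypothesis 3, a key secondary hypothesis. Second, nothing in the text keeps physicians balanced over the arms. Randomisation precedes the consultation, physicians are not blinded, and intervention patients spend about 35 minutes with the tablet shortly beforehand, so scheduling could link physician to arm. An analysis without physician has no defence against that.

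**Working it through.** **1. The plan's own figure.** The only stated sample size is for the primary outcome: "45 participants per group (total = 90) is sufficient to detect" d = 0.6 at two-sided 5% and 80% power. A two-sample t test (noncentral t) needs 44.6, hence 45 per group, with power 80.4%. The figure reproduces. No power is stated for strain or SDM, so no stated number is in error here.

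**2. Inputs that the protocol does not give.** Number of physicians, consultations per physician, how patients reach a physician, physician ICC and block size are all absent. Assumed: 4, 8 or 12 physicians; ICC 0.1, 0.2 or 0.4; blocks of 4; total SD 1. N = 92 is close to the 90 evaluable patients of the primary calculation; N = 128 is full recruitment.

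**3. Simulation.** 2000 trials per setting: patients randomised 1:1 in blocks within two centres, with a random physician effect. Four analyses were compared: Mann-Whitney on a 5-point score; regression on arm and centre; regression with physician fixed effects; and a rank test stratified by physician (van Elteren). Monte Carlo error at a true 5% is √(0.05 × 0.95 / 2000) ≈ 0.5 points.

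**4. Physicians see both arms, arm unrelated to physician, no true effect.** Over N = 92 and 128, 4 to 12 physicians and ICC 0.1 to 0.4:

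- Mann-Whitney rejects 4.0 to 5.5% of the time, and regression on arm and centre 4.5 to 5.8%.
- Mean model standard error divided by empirical SD of the estimate is 0.97 to 1.01.

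The planned analyses are valid here. Patient-level randomisation makes arm independent of physician.

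**5. Power in the same setting** (N = 92, 8 physicians, d = 0.5):

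| ICC | Mann-Whitney | Stratified rank test | Gain | Regression, arm + centre | Physician fixed effects | Gain |
|---|---|---|---|---|---|---|
| 0.1 | 60.5% | 59.8% | −0.7 | 67.5% | 67.2% | −0.3 |
| 0.2 | 62.6% | 66.1% | 3.5 | 69.1% | 72.5% | 3.4 |
| 0.4 | 62.9% | 76.1% | 13.2 | 71.5% | 83.9% | 12.4 |

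A hand check for a continuous score: without physician, SE ≈ 2/√92 = 0.209, and power ≈ Φ(0.5/0.209 − 1.96) ≈ 67%. Removing all physician variance multiplies the SE by √(1 − ICC). At ICC 0.4 this is 0.209 × √0.6 ≈ 0.162, and power ≈ Φ(0.5/0.162 − 1.96) ≈ 87%. The simulated 83.9% lies a little below this ceiling, as expected, because estimating eight physician effects costs some information.

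**6. Physicians unevenly spread over arms, no true effect** (N = 92, 8 physicians, assumed 75/25 tilt):

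| ICC | Mann-Whitney | Regression, arm + centre | Stratified rank test | Physician fixed effects |
|---|---|---|---|---|
| 0.1 | 8.0% | 9.3% | 5.2% | 5.7% |
| 0.2 | 9.6% | 9.6% | 4.9% | 4.7% |
| 0.4 | 16.5% | 19.2% | 4.7% | 4.8% |

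At ICC 0.4 the model SE is 0.196 against an empirical SD of 0.295, a ratio of 0.666. Then 2 × [1 − Φ(1.96 × 0.666)] ≈ 19%, which agrees with the simulated regression figure.

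**7. Cost if physicians hardly differ.** At ICC 0, with 128 consultations, 10 physicians and a shift of 0.4 SD (assumed; 3000 simulations), stratifying by physician loses 3 to 6 points of power. A random intercept largely avoids this.

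**The case against.** The strongest reply is that randomising patients individually already protects the planned tests, so what remains is a choice between a less and a more efficient analysis. That stands for the balanced case (step 4). A reader used to cluster trials might infer that the standard errors are wrong, or that precision is overstated, merely because ratings repeat within physician. The documents do not support that: with arm unrelated to physician, the standard error correctly describes the less efficient analysis.

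A reader might also infer that the plan ignores physician differences altogether. It does not: physician characteristics are collected as possible covariates, and the covariates of the OPTION-5 model are not listed and may be set elsewhere. The SDM part is therefore the weaker half. Adjusting for characteristics such as experience would still leave correlation within a physician.

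A third tempting argument is that the PtDA effect may differ between physicians. With a between-physician SD of the effect of 0.3 (ICC 0.2), Mann-Whitney rejects a zero average effect in 7.0% of trials and regression in 7.7%, but physician fixed effects reject in 8.9%. The proposed change does not address this, and the protocol does not claim inference to physicians in general, so the argument carries no weight here.

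Finally, it is not stated that the same physicians serve both arms. If each served one arm only, the planned tests would do worse (Mann-Whitney 16 to 42%, regression 18 to 46% error for ICC 0.1 to 0.4), and within-physician stratification would not be possible. Patient-level allocation at two centres makes that arrangement unlikely.

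**Conclusion.** The point holds in a limited form, and rests mainly on the Mann-Whitney choice, which the protocol states outright. That test treats ratings as coming from two independent groups of physicians, which the design does not produce, and it omits both physician and the centre stratum. For OPTION-5 the point is only that no physician term is named for an outcome that measures the physician.

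With physicians balanced over arms, the consequence is lost power that ranges from nothing (ICC 0.1) to 12 to 13 points (ICC 0.4). With a 75/25 tilt, which nothing in the text prevents, the error rate is about 8 to 19% instead of 5%. These sizes depend on the assumed ICC, number of physicians, effect and tilt, none of which the protocol gives. Only secondary outcomes are touched.

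**What to change.** 1. State how patients reach a physician, and record a physician ID for every consultation.
2. For strain, replace the Mann-Whitney test with a van Elteren rank test stratified by physician within centre, or with an ordinal (cumulative-logit) mixed model with arm and centre as fixed effects and a physician random intercept.
3. For hypothesis 3, name a physician effect in the OPTION-5 regression, alongside centre.
4. Reword the strain comparison as one between consultations of the two arms, not between groups of physicians.

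The cost is one ID variable and a few lines in the analysis plan; physician characteristics are already collected. Stratification loses a few points of power if the physician ICC is near zero, which the random intercept largely avoids. The random intercept was not itself run under the uneven-spread scenario; the error rates near 5% shown there are for stratification and fixed effects.

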## Discussion

In this study, we want to investigate whether an interactive web-based PtDA developed by our research group can effectively support patients with metastatic melanoma in their treatment decision. The main purpose of the PtDA is to empower patients by increasing their knowledge about different treatment options. In studies of patients with various types of cancer, including melanoma, it has been shown that patients have a very high need for information about the disease, treatments, procedures, side effects, and prognosis, especially directly after receiving diagnosis [23, 49–51]. A fulfilled need for information is associated with lower anxiety and depression levels in cancer patients [52]. In the current reality of melanoma care, medical consultation is the main source of information [53]. However, there is usually not enough time for an extensive educational discussion with the physician. Patients therefore have a tendency to inform themselves online, even though available German websites have a medium quality and are difficult to understand, according to reviewer-based assessments [54, 55]. The developed evidence-based PtDA is thus intended to close a gap in clinical care. We assume that a higher level of knowledge also facilitates a greater involvement of patients in the decision-making process in the sense of SDM and increases patients’ decision satisfaction with the course of the selected treatment.

As described above, the evaluation of the PtDA is to be carried out in a multicenter, randomized, controlled study design and comprises several measurement points (T_0_, T_1_, T_2_), since the influence of SDM in general, and presumably of PtDAs in particular, on patient satisfaction can only be expected over the long term [30]. Patients with access to the PtDA before the medical consultation will be compared with patients who receive treatment as usual. The study design is thus adapted to clinical care processes. On the one hand, this guarantees high external validity. On the other hand, this means that the study procedure cannot be extensively standardized. For example, we expect variations in the course of the medical consultation. Sources of this variance are physician-related variables (e.g., professional experience), patient-related variables (e.g., BRAF status), and setting-related variables (e.g., if including the patient in a drug trial is available as an additional option to the standard therapies). Additionally, different progressions after the decision for one treatment option between patients must be considered. It is possible, for example, that a patient may have to discontinue the selected therapy due to severe adverse events, and the follow-up survey T_2_ may therefore have to take place earlier. A further limitation of the design is the lack of the possibility of blinding group membership.

In summary, the project aims to close a relevant gap in the education and care of patients with metastatic melanoma by means of an interactive web-based PtDA. As we have shown, the therapeutic decision for metastatic melanoma is very complex, far-reaching, and partly preference-dependent. Especially with regard to the evaluation of novel immunotherapies, it is to be expected that patients will be overwhelmed by the task of understanding the complex mode of action of these therapies and weighing their various risks and benefits. It is known that a better subjective quality of care in oncological patients can be achieved by a stronger involvement of the patient in therapy decisions [56]. A PtDA empowers the oncological patient to take a more active role in the decision-making process [29] without additional time costs on part of the physician. A PtDA also provides important knowledge, e.g., on how to cope with side effects, which promises better treatment adherence [30]. However, the positive effects of PtDAs depend largely on their conceptual and technical implementation. In the planned evaluation study, proof of efficacy is to be provided under controlled conditions. On this basis, the PtDA can either be further optimized or, if successful, be disseminated throughout Germany.

## Data Availability

The datasets analyzed during the current study are available from the corresponding author on reasonable request. The data will be available after the main publication of them. Any data required to support the protocol can be supplied on request.

## Abbreviations

CG: Control group
CPS: Control Preferences Scale
EORTC: European Organization for Research and Treatment of Cancer
IG: Intervention group
IPDAS: International Patient Decision Aids Standards
ITT: Intention-to-treat
m. c.: Medical consultation
NCT: National Center for Tumor Diseases
PtDA: Patient decision aid
QQPPI: Questionnaire on the Quality of Physician-Patient Interaction (FAPI: Fragebogen zur Arzt-Patienten-Interaktion)
SDM: Shared decision-making
SPSS: Statistical Package for the Social Sciences
SwD: Satisfaction with Decision Scale
TAU: Treatment as usual
UCC: University Cancer Center
QLQ-C30: Quality-of-life Questionnaire
